### Secondary outcome measures

**Brief Symptom Inventory (BSI)** (73, 74): The BSI is a 53-item self-report scale that measures psychopathological and psychological symptoms present at the time of assessment. It uses a 5-point Likert scale to rate each item, and the scores cover nine dimensions: somatization, obsession-compulsion, interpersonal sensitivity, depression, anxiety, hostility, phobic anxiety, paranoid ideation, and psychoticism. These nine dimensions can be summed to yield three global indices (73). These synthetic indices are the general severity index (GSI), the positive symptom distress index, and the positive symptom total. Specifically, the BSI uses a 5-point Likert scale ranging from 0 (―not at all to 4 (―extremely). The Cronbach ‘s α for the instrument in total is.96 and ranges between.71 and.87 for its subscales (75).

**The World Health Organization Quality of Life (BREF)** (76, 77): The WHOQOL-BREF is a self-report questionnaire that is short and easy to administer and assesses 4 domains of quality of life (QOL): physical health, psychological health, social relationships, and the environment. In addition, there are 2 items that measure overall QOL and general health. The WHOQOL (Bref) is grouped into 4 domains of QOL and 2 items that measure overall QOL and general health: 1. Physical health, 2. Psychological health, 3. Social relationships 4. Environment. Cronbach’s alpha values for each of the four domain scores ranged from.66 (for domain 3) to.84 (for domain 1), demonstrating good internal consistency (76).

**Inventory of Interpersonal Problems (IIP–64)** (78). The IIP-64 refers to the interpersonal circumplex model (79–81), which has two separate dimensions that describe the quality and intensity of behavior between people. The IIP-64 names its scales *domineering*, *vindictive, cold, socially avoidant, submissive, exploitable, overly nurturing, and intrusive*. Researchers have demonstrated that the psychometric properties of the IIP-64 range from acceptable to good. A study by Vittengl, Clark, and Jarrett (82) on the English version revealed that the subscales were reliable (Cronbach’s alpha) between.72 and.88 and that they were reliable again after 20 sessions of cognitive therapy for depression, with scores of 0.79 for the DOM and 0.84 for the AFF. In our sector’s validation procedure of the IIP-64 (83), the statistical analyses revealed a valid and reliable tool (Cronbach’s α = .932).

**The Work and Social Adjustment Scale** (**WSAS)** (84). It is a self-report instrument that consists of 5 items that are scored on a scale ranging from 0 to 8. We assessed functional impairment in the domains of *work, household, social leisure, private leisure, and family and relationships at the time of assessment.* The reliability, validity and sensitivity to change of the WSAS have been firmly established in samples of patients with different clinical disorders (85, 86).

The World Health Organization Disability Assessment Schedule (WHODAS 2.0) (12, 87) is a standardized assessment tool developed by the World Health Organization that assesses disability-related health conditions in the past 30 days. The measure assesses disability across six domains: cognition, mobility, self-care, getting along with others, life activities, and participation. A profile of functioning is derived across the six domains, as is a general disability score. The WHODAS 2.0 has demonstrated excellent reliability and validity (12). Across the study samples, Cronbach’s α for the overall score of global functional disability was.97, with the domain scale scores ranging from.83 (self-care) to.94 (life activities).

**Treatment Retention:** Dropouts will be recorded. An assistant researcher will contact through telephone any patient who will drop out, and if she/he agrees, an interview will be conducted to elicit the patient’ s perspective about the intervention and the reasons for dropping out. The interviews were semi structured and were developed by the research group of the study.

### Mediators

**Reflective Functioning Questionnaire (RFQ**) (88, 89): This is a brief, screening measure of reflective functioning. It has been developed to assess severe impairments or imbalances in mentalizing, which are typically observed in patients with borderline personality disorder features. Through confirmatory factor analyses, the two factors—certainty (RFQ_C) and uncertainty (RFQ_U)—were found to be fairly different. They remained the same across clinical and nonclinical samples and had good internal consistency and test-retest stability. The RFQ has satisfactory reliability and test–retest reliability. The estimates of internal consistency for RFQ_U and RFQ_C were.77 and.65, respectively, in the clinical sample and.63 and.67, respectively, in the nonclinical sample. The test–retest reliability over a period of 3 weeks was excellent, with *r*
_s_ = .84 and.75 for RFQ_U and RFQ_C, respectively, all *p* =0.001 (88).

**Defense Style Questionnaire (DSQ-40)** (90): The 40-item version of the DSQ-40, derived from the original measure developed by Bond, Gardner, Christian, and Siegel (91), is a widely used self-report measure for defense mechanisms because of its easy administration and cost effectiveness. It aims to assess behavior indicative of conscious derivatives of defensive styles that correspond to hypothesized patterns of unconscious psychological mechanisms (90).

The **Inventory of Personality Organization (IPO)** (92, 93) is a self-report instrument intended to measure a patient’s level of personality organization. We constructed the scale to cover five personality dimensions, with the first three serving as the primary clinical scales. These scales assess the degree of identity pathology, the level of immature defensive mechanisms (Primitive Defenses, PD), and the degree of impairment in the ability to test reality (Reality Testing, RT). The three IPO scales demonstrate adequate internal consistency and good test–retest reliability. Lenzenweger (92) reported that the three main dimensions of an IPO’s first psychometric properties in adult and psychiatric samples are internally consistent: identity diffusion (α = .84–.90), reality testing (α = .85–.87), and primitive defenses (α = .80–.87). Confirmatory factor analysis at the item level supported a two-factor structure of the IPO, which is consistent with Kernberg’s model of borderline personality organization (92).

### Process indicators

Since treatment for BPD in both groups (intervention and TAU) is delivered in routine clinical practice, it might be considered as a complex intervention (94). Hence, it is hard to disentangle the effect of the content of the intervention, the intensity and the duration. Information about the number and type of sessions attended will be recorded and manipulated as confounder variables.

### Statistical analyses

#### Assessing the comparability of the two groups

Prior to the initiation of treatment, i.e., at baseline, the two groups will be compared for potential differences in all primary and secondary outcome variables: severity of BPD symptoms, self – harm and suicidality, severity of psychopathological symptoms, quality of life, quality and intensity of interpersonal relationships, functioning and disability. Due to being many outcome variables, MANOVA will be employed. Moreover, the two groups will be compared for potential differences in various socio-demographic variables as well as the presence of physical illness and details of the medication regime for BPD, by employing t-tests for independent samples. In line with this, socio-demographic and other variables that are significantly different between the two groups will be considered to be confounder variables and will be inserted as such in all ensuing analyses.

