**Figure 1 f1:**
[figure not shown]
Flowchart of the study design.

Primary outcomes will be (i) the severity of BPD symptoms and (ii) the severity of self-harm and suicidality. Secondary outcomes will be: (i) psychopathological symptom severity, (ii) quality of life, (iii) quality and intensity of interpersonal relations, (iv) functioning and (v) disability.

Mediator variables will be: (i) reflective functioning, (ii) defense style and (iii) personality organization. In other words, better primary and secondary outcomes for the intervention group as opposed to TAU group are expected to be discerned due to differences in reflective functioning, defense style and personality organization. As the design does not include random allocation of participants in the two arms, baseline measurements of the outcome variables will be considered as confounders for the ensuing measurements. Moreover, the two groups will be compared in terms of the following variables: sex, family status, education status, number of children, profession, living arrangement, physical illness, medication for BPD and prior hospitalize physical illness, medication for BPD and prior hospitalization. Those variables with a statistically significant difference between the two groups, will be considered confounder variables in the design and will be taken into consideration as such in ensuing evaluation points. Moreover, information about the treatment delivered in the two groups will be recorded; namely, duration of treatment, type and number of sessions attended. These will be included as confounder variables in the design.

The Ethics Committees of Eginition Hospital, Medical School of the National and Kapodistrian University of Athens (No. 404/05-07-2021), Attikon Hospital (No. 443 25/08/2021), and Sismanogleion General Hospital (27703/10-12-2021) approved the research protocol. The Clinical Trials.gov website has registered the trial under the ID NCT06392139 (Protocol ID No. 404/06-07-202).

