### Sample size

Based on the power analysis (power=0.90), we estimated that the sample size of our study should be 212 participants (106 people per group) to detect differences between the two clinical groups. The power calculation was based on a moderate effect size (Cohen’ s d= 0.45) due to the naturalistic character of the study. A recent meta-analysis (58) established this value of Cohen’s d, calculating the effect size for borderline symptom trials as either 0.31 or 0.56, depending on the stand-alone or add-on design. Accessing these data, the authors decided to set the effect size as 0.45, which is a moderate value that is neither strict nor lenient. Before we reach the aforementioned sample size, we start processing our data within subjects, where a smaller sample size of 158 participants (79 per group) is needed to obtain a significant power of 0.80. The software used to calculate the power was R version 4.0.3.

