#### Evaluation of effect

For evaluating the effect of the group assignment (intervention *vs* control) on the primary and secondary outcome variables, multiple linear regression models will be computed for each outcome variables. As predictors the following variables will be inserted: the baseline measurement of the outcome variable of interest, treatment duration, number of sessions attended and all variables that emerged as confounders at baseline (i.e. socio-demographic and other variables that were significantly different across groups).

This analysis will be replicated for all evaluation time points: T_1_ – T_4_. For time points T_6_-T_10_, it will occur only for the two primary outcome variables.

At the end of the study, a Repeated Measures ANOVA with the group assignment (IV) and the 11 time points of assessment (baseline, T_1_ – T_10_) will be performed for the two primary outcome variables.

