#### Dropout rates

Dropout rates will be compared at the end of the study with the non-parametric criterion Mann Whitney (IV: group assignment and DV: number of drop outs), as number of drop-outs is an ordinal variable.

The Statistical Package for the Social Sciences (SPSS) version 25 (95) will be used for the statistical analyses. All significance tests will be two-tailed, with a 5% significance level and 95% confidence interval.

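### Baseline t-tests on nominal variables with three or more categories depend on how the categories are numbered, so a real imbalance can be missed and the variable left out of the effect models

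*Protocol article*

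**What the plan says.** In the protocol article, under Assessing the comparability of the two groups, one sentence covers the socio-demographic variables "as well as the presence of physical illness and details of the medication regime for BPD, by employing t-tests for independent samples". The t-test governs everything in that sentence, including the socio-demographic variables named just before these words. No other test is named for them.

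The Design section lists what is compared: "sex, family status, education status, number of children, profession, living arrangement, physical illness, medication for BPD", and prior hospitalisation. The same section sets the selection rule: "Those variables with a statistically significant difference between the two groups, will be considered confounder variables in the design". The comparability section repeats it, saying that variables found to differ significantly "will be considered to be confounder variables and will be inserted as such in all ensuing analyses". Under Evaluation of effect, the regression predictors are the baseline value of the outcome, treatment duration, number of sessions, and "all variables that emerged as confounders at baseline (i.e. socio-demographic and other variables that were significantly different across groups". The test level is given under Dropout rates: "All significance tests will be two-tailed, with a 5% significance level and 95% confidence interval".

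**The concern.** Family status, profession and living arrangement have no natural order. If one of them is held as a single code with three or more values, the t-test asks whether the mean code is equal in the two groups. The question that matters is whether the groups have the same mix of categories. The two questions can have different answers, and the first changes when the same patients' categories are renumbered.

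This is more than a descriptive table. Allocation is not random, and the significance screen is the only stated route by which a socio-demographic variable enters the main-effect models as a confounder. Recruitment and Limitations and challenges say that the TAU centres serve areas with different socio-economic characteristics, so imbalance in these variables is plausible. If the screen misses an imbalance, the group effect carries whatever part of it the other covariates do not remove.

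**Working it through.** **Inputs from the protocol.** 106 per group (Sample size), two-sided 5% (Dropout rates), planning effect d = 0.45 (Sample size). The article gives no category shares, so those below are assumptions.

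**The plan's own figure.** n per group = 2 × (1.96 + 1.2816)² / 0.45² = 2 × 10.508 / 0.2025 = 103.8, so 104. The exact t calculation gives 104.7, so 105. The stated 106 is consistent with this and is used below.

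**One table by hand.** Take counts of 37/32/37 in one group and 21/64/21 in the other.
- Codes 1, 2, 3: mean codes are (37 + 64 + 111)/106 = 2.00 and (21 + 128 + 63)/106 = 2.00. So t = 0.00, p = 1.00.
- Chi-square, expected counts 29/48/29: 4 × 8²/29 + 2 × 16²/48 = 8.83 + 10.67 = 19.5 on 2 df, p = 0.00006.
- Same patients, codes 1 and 2 swapped: means are 217/106 = 2.05 and 169/106 = 1.59, t = 4.09, p = 0.00006.

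**Detection rates, three categories.** Assumed shares A/B/C are 50/30/20% against 60/10/30%. Chi-square power is about 94% by simulation under any numbering. For the t-test, the ratio is the difference in mean codes divided by √[(v1 + v2)/106], where v1 and v2 are the code variances.

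| Codes A, B, C | Mean codes | v1, v2 | Ratio | t-test power |
|---|---|---|---|---|
| 1, 2, 3 | 1.7 v 1.7 | – | 0 | about 5% |
| 2, 1, 3 | 1.9 v 2.2 | 0.49, 0.36 | 0.30/0.0895 = 3.35 | about 91% |
| 1, 3, 2 | 1.8 v 1.5 | 0.76, 0.45 | 0.30/0.1068 = 2.81 | about 80% |

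**Detection rates, four categories.** Assumed shares are 25% each against 37/13/13/37%. Mean codes are 2.5 in both groups. The t-test detects the imbalance in about 5% of trials, chi-square in 88%.

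**Checks.**
- With equal distributions, both tests reject at about 5%.
- For a two-category variable, 50% against 30%, both detect the difference in 85% of trials, so nothing is lost.

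**How typical the worst cases are.** The 5% figures come from shares chosen so that the mean codes coincide. With randomly drawn shares for 3–5 categories, restricted to imbalances that chi-square would find with 80–98% power, the t-test found 50–59% on average. It fell below 20% in about a quarter of them (24–27%). These figures move with the number of categories and the way the shares are drawn.

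**Possible bias after a miss.** Bias = imbalance × prognostic gap. With an assumed 20-point imbalance and 0.5 SD gap, this is 0.20 × 0.5 = 0.10 SD, or 0.10/0.45 = 22% of the planning effect. The models also contain the baseline outcome. If that removes a share r of the bias, 0.10 × (1 − r) remains:
- r = 0.4: 0.06 SD (13% of 0.45)
- r = 0.7: 0.03 SD (7% of 0.45)

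**The case against.** The article does not say how these variables are coded. If family status, profession and living arrangement are each held as two categories (for example, partnered or not), the t-test and chi-square agree in practice and there is no fault. This stands, and it makes the point conditional on three or more categories.

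A reader might infer several stronger things that the article does not support:
- **That the t-test is wrong for every variable in the list.** It is harmless at this sample size for sex, presence of physical illness and other two-category items, and acceptable for number of children.
- **That the medication comparison is also faulty.** The article speaks of medication and details of the regime. That could be a yes/no item, a count or a set of categories, so no fault can be shown.
- **That imbalances will usually be missed.** Near-total loss occurs only when the mean codes happen to coincide or nearly so.
- **That the treatment effect will be biased by about a fifth of d = 0.45.** That needs a miss, an assumed prognostic gap, and a category that affects follow-up but is unrelated to baseline severity. Adjustment for the baseline outcome would usually shrink the bias.

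Two other defences carry less weight. Limitations and challenges says that a statistician will be consulted and that more robust methods are needed, but the stated test remains in the text. It can also be said that selecting confounders by significance is the larger weakness and that fixing the covariates in advance would make the choice of screening test irrelevant. That is true, but it is a separate point. While the screen is kept, its test has to suit the variable.

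**Conclusion.** The point holds in a limited form. The protocol fixes a t-test for all socio-demographic variables, and at least three of those listed are nominal. Where such a variable is analysed with three or more categories, the screen depends on arbitrary numbering and can leave a genuinely imbalanced variable out of the effect models.

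In the assumed worst cases the loss is from 88–94% detection to about 5%; the average loss is smaller. Any resulting bias depends on how far the variable predicts outcome beyond the baseline measurement. Under the assumed 20-point imbalance and 0.5 SD gap it is 0.10 SD at most, and about 0.03–0.06 SD if baseline adjustment removes 40–70%. The category shares, the gap and the removal fraction are all assumptions. The correction should be made because it is simple and this step decides the covariate set, but the documents do not show that the result would be seriously distorted.

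**What to change.** Under Assessing the comparability of the two groups, keep t-tests for continuous variables (and, harmlessly, two-category ones). Compare nominal variables on their category distribution by chi-square, or by Fisher's test where cells are sparse, as may happen with profession. Report standardised differences by category. Under Evaluation of effect, state that nominal confounders enter as indicator variables and not as a single code.

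This takes one sentence in each section and no new data. The cost is a few more degrees of freedom when a nominal variable enters a model.

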#### Evaluation of effect

For evaluating the effect of the group assignment (intervention *vs* control) on the primary and secondary outcome variables, multiple linear regression models will be computed for each outcome variables. As predictors the following variables will be inserted: the baseline measurement of the outcome variable of interest, treatment duration, number of sessions attended and all variables that emerged as confounders at baseline (i.e. socio-demographic and other variables that were significantly different across groups).

This analysis will be replicated for all evaluation time points: T_1_ – T_4_. For time points T_6_-T_10_, it will occur only for the two primary outcome variables.

At the end of the study, a Repeated Measures ANOVA with the group assignment (IV) and the 11 time points of assessment (baseline, T_1_ – T_10_) will be performed for the two primary outcome variables.

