We designed this study to evaluate the effectiveness and economic aspects (cost-effectiveness and cost-utility) of the STP-BPD in everyday clinical practice, adhering to the call for *‘real-world’* clinical trials (55, 56). Therefore, we will use minimal exclusion criteria without altering clinical decision-making, health care, or treatment. Patients will be followed for 2 years for primary and secondary outcomes, and for additional 3 years for primary outcomes only. Assessment of the clinical and psychosocial outcome variables will be performed at baseline (T_0_), prior to patient allocation, and every 6 months until the end of the 2^nd^ year of follow-up (T_1_, T_2_, T_3_, and τ_4_). At baseline (T0) and then every year thereafter (τ2 and τ4), the mediators that affect the link between the type of health care service and the major clinical and psychosocial outcomes will be examined. For long-term evaluation, primary outcome variables will also be assessed at T_5_ (2 years and 6 months), T_6_ (3 years), T_7_ (3 years and 6 months), T_8_ (4 years), T_9_ (4 years and 6 months) and T_10_ (5 years). Patient flow, screening and assessments are displayed schematically in **Figure 1**.

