## Limitations and challenges

Participants could not be randomly allocated to the two arms, as the study was aiming to evaluate the effectiveness of BPD treatment in routine clinical practice conditions (feasibility reasons underlay opting for quasi experimental design rather than an RCT). As a result of this, the comparability of the two groups (intervention *vs* control) is questioned in these designs, especially in terms of selection bias and confounding variables. Patients with BPD from both groups were recruited from services affiliated with hospitals (outpatients departments of hospitals treating patients with BPD), rather than from community mental health centers, in order to keep the severity of BPD at similar levels. Hence, the two services of the control group were selected because they also treat patients with severe forms of BPD and because they are located at different regions of Athens area, with different socio-economic backgrounds. In line with this, it was assumed that the severity of BPD would be comparable across groups as well as their socio-economic background (and pertinent environmental stressors). Differences in baseline measurements between the two groups will be explored in order to confirm or refute the presence of statistically significant differences between the two groups in the outcomes of interest at baseline, that is prior to the initiation of the intervention. Baseline differences will be inserted as a confounder variable in ensuing evaluations (T1 – T10). Moreover, differences between the two groups in terms of cardinal socio-demographic variables and medication regime variables will be explored. Variables that will be substantially different between groups will be considered confounders. Due to timeline constraints, consultation with a statistician is planned for the next stages of the project; this limitation is acknowledged, along with the need to apply more contemporary and robust analytical approaches.

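### The visit-by-visit adjusted regression for the two primary outcomes skips T5 (2 years 6 months) without a reason, although T5 is scheduled and is in the end-of-study ANOVA

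*Protocol article*

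**What the plan says.** Four places in the protocol article bear on T5.

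- **Design** sets the long-term visits: "For long-term evaluation, primary outcome variables will also be assessed at T_5_ (2 years and 6 months), T_6_ (3 years"), and so on every six months to T10 at 5 years. Table 1 (Participants) agrees: the BPDSI and the Suicide and Self-Harm Inventory are ticked at every visit from T0 to T10, T5 included.
- **Evaluation of effect**, on the regression for each outcome, gives two ranges. The first is "This analysis will be replicated for all evaluation time points: T_1_ – T_4". The second is "For time points T_6_-T_10_, it will occur only for the two primary outcome variables". T5 is in neither.
- **Evaluation of effect**, next paragraph, plans a repeated measures ANOVA by group at the end of the study, with "the 11 time points of assessment (baseline, T_1_ – T_10_) will be performed for the two primary outcome variables". T5 is included here.
- **Limitations and challenges** describes the adjustment without a gap: "Baseline differences will be inserted as a confounder variable in ensuing evaluations (T1 – T10").

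Two further statements matter. The moderation text, under Mediation analysis, adds a group-by-age interaction to the regressions described under Evaluation of effect, so that term exists only at visits where the regression is run. Assessing the comparability of the two groups says that variables differing at baseline will enter all later analyses.

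**The concern.** The article fixes the list of visits for its adjusted model, and that list does not match its own schedule. This is not a detail left to an unseen analysis plan: both ranges are stated, and one scheduled visit falls between them.

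Allocation is not random, and the article names confounding as its main limitation. The per-visit regression is the analysis for which it spells out adjustment for the baseline value, treatment duration, number of sessions and baseline confounders. T5 is the first visit after the 2-year phase, so it gives the first reading of whether a difference seen at T4 persists. Followed literally, the series of visit-specific adjusted estimates steps from month 24 (T4) to month 36 (T6). The Suicide and Self-Harm Inventory looks back six months and visits are six months apart, so the T6 interview does not recover what the T5 interview records for months 24 to 30.

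An unresolved range also leaves open, once long-term data are in hand, whether a T5 estimate is reported.

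**Working it through.** **Visits scheduled against visits analysed, for each primary outcome**

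| Source in the protocol article | Follow-up visits | Is T5 in? |
|---|---|---|
| Design; Table 1 | T1–T10 (10 visits) | Yes |
| Evaluation of effect, per-visit regression | T1–T4 and T6–T10 | No |
| Evaluation of effect, repeated measures ANOVA | baseline and T1–T10 | Yes |
| Limitations and challenges, baseline adjustment | T1–T10 | Yes |

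1. The plan's own count first. Baseline plus T1 to T10 is 1 + 10 = 11, which matches the 11 time points stated for the ANOVA. The ANOVA therefore includes T5.
2. Visits with a per-visit regression: 4 (T1–T4) + 5 (T6–T10) = 9.
3. Scheduled follow-up visits less visits with a regression: 10 − 9 = 1, and that visit is T5.
4. Share missed: 1/10 = 10% of follow-up visits, and 1/6 = 17% of the long-term visits T5–T10.
5. After the change to T5–T10: 4 + 6 = 10 regressions per primary outcome, that is 9 + 1. Over two primary outcomes this adds 2 regressions. The ANOVA stays at 11 time points.

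**What T5 lacks as written.** It lacks the regression with the baseline value, treatment duration, sessions attended and baseline confounders, and with it the group-by-age term. It does not lack a group comparison, because the ANOVA has group as a factor and T5 as one of its levels of time.

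**Can the ANOVA stand in for the regression at T5?** Only in part. It treats all 11 visits together, and no T5-specific adjusted estimate is described from it. A standard repeated measures ANOVA also uses only patients with data at every visit. The article gives no missingness rate, so the following is an assumption: independent loss with probability p at each of 10 follow-up visits, baseline complete, 212 patients enrolled.

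Complete at all visits = 212 × (1 − p)^10

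- p = 2%: 0.98^10 ≈ 0.82, about 173 patients
- p = 5%: 0.95^10 ≈ 0.60, about 127 patients
- p = 10%: 0.90^10 ≈ 0.35, about 74 patients

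A regression at T5 would use everyone seen at T5.

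**Sample size.** The Sample size section states: "Based on the power analysis (power=0.90), we estimated that the sample size of our study should be 212 participants (106 people per group"), at d = 0.45. With two-sided 5% significance, n per group = 2(1.960 + 1.282)²/0.45² ≈ 103.8, so 104, or 105 by the t-test. The stated 106 gives power of about 0.90. No visit list enters this formula, so the T5 question does not affect it.

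**The case against.** The strongest reply is that this is a slip in a range that any reader can repair. The schedule, Table 1, the ANOVA sentence and the limitations text all run through T5, so T5–T10 was almost certainly meant. Scheduling a visit does not by itself oblige the authors to fit a separate regression there. The primary aim is the 2-year follow-up at four time points, which is untouched. All of this stands, and it sets the weight of the point. It does not make the sentence right: the sentence is an operative analysis rule, and a rule followed literally omits T5.

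Several stronger readings are tempting, and the documents do not support them.

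- *T5 yields no group comparison at all.* It does yield one. The repeated measures ANOVA, under the same heading, has group and all 11 time points.
- *T5 appears in no adjusted analysis.* This is not established. The ANOVA sentence lists no covariates, but the section on comparability sends baseline confounders into all later analyses, and Limitations and challenges extends baseline adjustment to T10. Some adjustment of the ANOVA may be intended. What is clearly missing is the visit-specific regression.
- *The inventory at T5 is the only record of self-harm and suicidality in months 24 to 30.* The BPDSI is also given at T5, covers the past three months and has a parasuicidal domain. It therefore covers part of that window, though not admissions.
- *212 patients × 2 instruments = 424 assessments go without a visit-specific regression.* That assumes nobody is lost by 2.5 years, whereas the Aims section expects losses at longer follow-up. It is a ceiling and not an estimate.

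**Conclusion.** The point holds as a minor inconsistency in a stated analysis rule. The per-visit adjusted regression for the two primary outcomes covers 9 of 10 scheduled follow-up visits and omits T5 without explanation, while the schedule, Table 1, the limitations text and the ANOVA all include T5. The consequence is one missing visit-specific adjusted estimate for each primary outcome, and the missing group-by-age term at that visit. It is confined to the longer-term evaluation. The 2-year primary aim, the sample size and the power are not affected.

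The count rests only on the visit labels as printed. That the omission is a slip is an inference from the surrounding text. The figures for complete cases in the ANOVA rest on assumed loss rates and serve only to show why the ANOVA is not a full substitute.

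**What to change.** Under Evaluation of effect, change the second range from T6–T10 to T5–T10, so that it agrees with Design, Table 1 and Limitations and challenges. If T5 was left out on purpose, say so there and give the reason. Settle this before the long-term data are analysed.

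The cost is one more regression per primary outcome (9 becomes 10), on data the schedule already collects. No new assessments are needed, and neither the sample size nor the ANOVA changes.
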